## Study Protocol for Ethical Approval

### Impact of human filarial infections on the metabolic and immunological profile

|                             |                                                                                       |
|-----------------------------|---------------------------------------------------------------------------------------|
| Version:             | 4.3; March 2023                                                                |
| Acronym:             | FIMMIP                                                                         |
| Study centre:        | Department of Microbiology and Parasitology (DMP), University of Buea, Buea, Cameroon |
| Study design:        | Cross-sectional study                                                                 |
| Study area:          | Littoral region in Cameroon                                                           |
| Funding:             | DFG German-African Cooperation Projects in Infectology                                |
| Grant Number:        |                                                                                       |
| Proposed start date: | December 2019                                                                         |
| Proposed end date:   | December 2026                                                                         |

### 3 PROTOCOL SYNOPSIS

|                               |                                                                                                                                                                                                                                                                                                                                                                                                                                                                                                                                                                                                                                                                                                                                                                                                                                                                                                                                                                                                                                                                                                                                                                                                                                                                               |
|-------------------------------|-------------------------------------------------------------------------------------------------------------------------------------------------------------------------------------------------------------------------------------------------------------------------------------------------------------------------------------------------------------------------------------------------------------------------------------------------------------------------------------------------------------------------------------------------------------------------------------------------------------------------------------------------------------------------------------------------------------------------------------------------------------------------------------------------------------------------------------------------------------------------------------------------------------------------------------------------------------------------------------------------------------------------------------------------------------------------------------------------------------------------------------------------------------------------------------------------------------------------------------------------------------------------------|
| Protocol Title         | Impact of human filarial infections on the metabolic and immunological profile                                                                                                                                                                                                                                                                                                                                                                                                                                                                                                                                                                                                                                                                                                                                                                                                                                                                                                                                                                                                                                                                                                                                                                                                |
| Participants           | 
Healthy male and female volunteers:
 
 
aged 18-60 years
 
BMI <math>\geq 25</math>, <math>< 25</math>
 
last intake of ivermectin (IVM) more than 4 months ago
 
last intake of anti-filarial antibiotic treatments more than 12 months ago
 
Residents of the endemic area for at least 5 years
 
                                                                                                                                                                                                                                                                                                                                                                                                                                                                                                                                                                                                                                                                                                                                                                                                                                                                                         |
| Number of participants | 1200 included in study (approx. 5000 will be screened)                                                                                                                                                                                                                                                                                                                                                                                                                                                                                                                                                                                                                                                                                                                                                                                                                                                                                                                                                                                                                                                                                                                                                                                                                        |
| Study design           | Interventional <del>randomized-controlled</del> open label pilot trial                                                                                                                                                                                                                                                                                                                                                                                                                                                                                                                                                                                                                                                                                                                                                                                                                                                                                                                                                                                                                                                                                                                                                                                                        |
| Study groups           | 
Group 1: Mansonella patients
 
 
Positive for Mansonella perstans
 
Microfilariae (Mf) positive and/or M. perstans PCR positive
 
BMI <math>\geq 25</math> (n =200)
 
BMI <math>< 25</math> (n =200)
 
 
Group 2: Onchocerciasis patients
 
 
Positive for Onchocerca volvulus
 
Microfilariae (Mf) positive and/or O. volvulus PCR positive
 
BMI <math>\geq 25</math> (n =200)
 
BMI <math>< 25</math> (n =200)
 
 
Group 3: Endemic normal
 
 
Mf negative in skin and blood
 
O. volvulus and M. perstans PCR negative
 
Negative for other filarial and helminth infections
 
Normal range of eosinophils and IgE levels
 
BMI <math>\geq 25</math> (n =200)
 
BMI <math>< 25</math> (n =200)
 
 
Group 4: Loiasis patients
 
 
Positive for Loa loa
 
Microfilariae (Mf) positive and/or Loa loa PCR positive
 
BMI <math>\geq 25</math> (n =200)
 
BMI <math>< 25</math> (n =200)
 
 |
| Treatment              | 
Doxycycline:
 
 
All individuals of group 1 and 2 as well as double infected individuals (Loa loa in addition to either O. volvulus or M. perstans) will be selected for doxycycline therapy
 
Daily doxycycline therapy for 6 weeks with 200mg
 
Individuals with <math>< 50</math>kg will receive 100mg doxycycline daily for 6 weeks
 
Individuals with <math>< 40</math>kg are excluded
 
                                                                                                                                                                                                                                                                                                                                                                                                                                                                                                                                                                                                                                                                                                                                                                       |

|                    |                                                                                                                                                                                                                                                            |
|--------------------|------------------------------------------------------------------------------------------------------------------------------------------------------------------------------------------------------------------------------------------------------------|
|                    | Albendazole: 
 
• Community based mass drug administration for group 1, 2, 3 and 4
 
• Individuals will receive one dose of 400mg Albendazole every three months with a total of 4 treatments
 
 |
| Time period | 2019-2026                                                                                                                                                                                                                                                  |

## 4 INTRODUCTION

### 4.1 Summary

Parasitic filarial nematodes modulate the host's immune system to enable their long-term survival within the host. This immunomodulation by helminths impacts the immune response of the host to bystander antigens and mitigates allergies and autoimmune diseases by suppressing associated pro-inflammatory immune responses. Such chronic, low grade pro-inflammatory immune responses also occur during obesity and are an important etiological factor for the pathogenesis of type 2 diabetes (T2D). Recently, experimental animal studies from our lab demonstrated that infections with the filarial nematode *Litomosoides sigmodontis* have a beneficial impact on diet-induced glucose intolerance and a similar protective effect was observed for other helminth infections in experimental animal studies and cross-sectional human studies. In this proposal, we aim to analyze the impact of human filarial infections *Onchocerca volvulus*, *Loa loa* and *Mansonella perstans* on the metabolic profile in association with changes in the systemic soluble and cellular immune response. In this regard, we will analyze glycaemia, lipid profile, liver function enzymes, adipocytokines, pancreatic and gut hormones, and the level of insulin resistance in obese individuals and compare it to lean individuals. A detailed analysis of the peripheral blood cell composition, intracellular cytokine-producing cells, cytokines/chemokines in plasma and released after *in vitro* whole blood stimulation, as well as total and filariae-specific humoral responses will be performed. Those responses will be compared to obese and lean endemic controls and followed-up after anti-filarial treatment with doxycycline for the *Mansonella* patients and onchocerciasis patients. All participants including endemic controls and *Loa loa* infected individuals will receive 4 rounds of albendazole.

### 4.2 Background

Parasitic helminth infections remain a public health problem in developing countries of the tropics and subtropics. Infections with *Onchocerca volvulus* can cause severe dermatitis, visual impairment and vision loss and it is estimated that approx. 17 million people are currently infected with *O. volvulus*, with 99% of all cases occurring in sub-Saharan Africa. *Mansonella perstans* on the other hand leads to infections that are often clinically silent and it is estimated that 120 million people are infected with *M. perstans*. Previous studies in Cameroon, which were in part done in collaboration between the two partner institutes (IMMIP, University Hospital of Bonn and the DMP, University of Buea) as part of a different DFG-Africa infectology project (Map2Co), revealed that infections with those helminths are endemic in the study area used in Cameroon.

Helminths generally induce in their hosts type 2 immune responses that are characterized by elevated type 2 cytokines, increased levels of IgE and IgG4 as well as an eosinophilia. Over time, helminths establish regulatory responses via the expansion of alternatively activated macrophages, regulatory T cells and the release of anti-inflammatory IL-10 & TGF $\beta$  in their hosts that enable their long-term survival in the human host, but also impact bystander immune responses. Previously, several human and experimental animal studies demonstrated that helminth infections prevent or ameliorate dysregulated immune diseases like autoimmune diseases, sepsis and allergies. A similar protective effect was recently suggested for metabolic diseases like T2D (1-11).

T2D is a growing challenge for health care systems in Africa. 80% of diabetes cases occur in low and middle income countries (12) and the largest increase of diabetes cases is expected to take place in regions with developing economies due to associated changes in life style and environment (12). Lack of awareness, health

care facilities and expenditure in underdeveloped countries has led to diabetes becoming a major problem. In Cameroon more than half a million patients suffer from diabetes. However, their diabetes related expenditure amounts to only 123 US\$/person in comparison to >5000 US\$/person in Germany (12). These figures strongly claim that diabetes is one of the major causes for global mortality, morbidity and health care expenditures, which will aggravate especially in Africa, where around 67% of diabetic subjects are undiagnosed and it is predicted that until 2035, the number of diabetes patients will more than double (12).

Several experimental studies by our group and colleagues support the protective role of helminth infections and helminth-derived products on type 1 diabetes (13-17). Obesity-induced inflammation is a primary etiological factor for the pathogenesis of T2D (18-20) and cell types associated with type 1 inflammation like classically activated macrophages, Th1 cells, neutrophils, NK cells and CD8 T cells are implemented in the pathogenesis of insulin resistance (21-26). Thus, helminth-induced type 2 and regulatory immune responses may counteract type 1 driven inflammation and it can be speculated that helminth infections have a beneficial impact on metabolic diseases such as T2D. Cross-sectional studies on humans and mechanistic studies on obese animal models published in the last few years suggested such a beneficial role of helminth infections on T2D. For instance, an epidemiological study in south India showed that prevalence of lymphatic filariasis decreased with the progression of glucose intolerance (1). Similarly, a history of *Schistosoma* infection was negatively associated with several glycemic parameters in a cross-sectional study in a rural community in China (2). A negative association between diabetes prevalence and *Strongyloides stercoralis* infection was observed in Australian Aboriginals (3). In Flores Island, Indonesia, individuals with soil transmitted helminth infections had a lower homeostasis model assessment of insulin resistance (HOMA-IR) and body mass index (BMI) (4).

Consistent with these human studies, a series of mechanistic studies in diet-induced obese mice revealed that helminth infections/helminth derived product administration induced protective type 2 immune responses, expanded eosinophils, ILC2s and AAM (5-7). This correlated with reduced glucose intolerance, hepatic steatosis and in some cases decrement in body weight and adipose tissue mass (8). Identified protective immune responses included the mitigation of adipose inflammation partly through IL-10 and suppressed hepatic lipogenesis (9), the triggering of the IL-33/ILC2 axis (10), induction of eosinophil and AAM expenditure in adipose tissue (6) and eventually stimulation of adipose tissue browning as type 2 immune responses are a promoter of browning, which increases energy expenditure (13, 27).

Besides the mentioned cross-sectional reports on humans and mechanistic studies on animal models, there is no longitudinal follow-up study that investigated the causal link between helminth infections, immunomodulation and metabolic responses. In light of the enormous global diabetes burden and the beneficial effect of helminth-induced immunomodulation on diabetes, it is important to elucidate the effect of helminth infections and their eradication on diabetes. Therefore, we aim to decipher the influence of immunomodulation by infections with the filarial nematodes *Mansonella perstans*, *Loa loa* and *Onchocerca volvulus* on glycemic and metabolic parameters in Southwest Cameroon, an endemic area for filarial infections.

### 4.3 Rationale

Clinical immunological studies in obese humans will decipher the impact of infections with the filariae *Mansonella perstans*, *Loa loa* and *Onchocerca volvulus* on glycaemic and metabolic parameters and associate

those with the systemic immune profile. Comparison to lean infected individuals as well as obese and lean endemic controls and follow-up analyses after anti-filarial treatment will determine the longevity of the filarial immunomodulation and indicate whether MDA programs to eliminate helminth infections may facilitate the development of T2D.

In brief, blood samples from *Mansonella* patients (Group 1), onchocerciasis patients (Group 2), *Onchocerca* and infection-free endemic individuals (Group 3) and *Loa loa* infected individuals will be assessed for glycemic and metabolic parameters and immune profiling will be performed. Each group will consist of 200 lean and 200 obese individuals. We aim to identify if there is

- i) an association between filarial infection, immunological responses and the glycaemic and metabolic profile and
- ii) whether anti-filarial treatment alters the immunological responses and the glycaemic and metabolic profile.

## 5 OBJECTIVES

### 5.1 Primary objective

Investigation for associations between a human filarial infection, the systemic immune response as well as the metabolic and glycemic profile

### 5.2 Secondary objective

The longevity of the filarial immunomodulation and its impact on the systemic immune response also on the metabolic and glycemic profile will be determined following anti-filarial treatment.

## 6 STUDY DESIGN

### 6.1 Study site

Within this proposed study a cohort will be collected, consisting of lean and obese endemic controls (group 3) and lean and obese individuals infected with either *M. perstans*, *Loa loa* or *O. volvulus* (groups 1,2 and 4). This study will be conducted in the Littoral region of Cameroon, an endemic area of *Onchocerca volvulus*, *Loa loa* and *Mansonella perstans*.

### 6.2 Estimated duration of the study

Recruitment of patients and sample collection will begin as soon as the ethical clearance of the revised protocol has been obtained with the aim of beginning in December 2019 as the funds have already been received from the DFG. Treatments with doxycycline and albendazole will be performed as soon as the ethical clearance of the newly revised protocol was obtained. The study comprises several stages, consisting of information of the regional health authorities, districts and communities, recruitment of volunteers, sample collection, sample processing, sample transport/export, data collection and analysis followed by preparation of publications. The patients will be followed for a period of 3 years, in 12-month intervals. It is estimated that the study will run until the end of December 2026.

### 6.3 Group allocation

Volunteers of both sexes (stratified according to age, gender and socio-economic status) with a BMI above  $\geq 30$  (obese) and  $< 25$  (lean), will be assigned to the following groups according to the clinical assessment (Fig. 1):

- 200 obese and 200 lean individuals with onchocerciasis (presence of microfilariae in the skin, *O. volvulus* PCR positive). All onchocerciasis patients will be treated with 200mg doxycycline daily for 6 weeks. They will also receive single dose of 400 mg albendazole every three months with a total of 4 treatments. *M. perstans*, *O. volvulus* as well as *Loa loa* co-infected individuals will be included and treated with doxycycline and albendazole, in case that not sufficient individuals with *O. volvulus* infection alone are identified.
- 200 obese and 200 lean individuals with *M. perstans* (presence of microfilariae in the blood, PCR positive). All *M. perstans* infected obese and lean patients will be randomly selected for anti-filarial therapy with 200mg of doxycycline daily for 6 weeks. They will also receive single dose of 400 mg albendazole every three months with a total of 4 treatments. *M. perstans* and *O. volvulus* as well as *Loa loa* co-infected individuals will be included and treated with doxycycline and albendazole, in case that not sufficient individuals with *M. perstans* infection alone are identified.
- 200 obese and 200 lean *Loa loa* infected and 200 obese and 200 lean healthy endemic individuals without onchocerciasis, *Mansonella perstans* infection with normal eosinophil counts and IgE levels. All endemic individuals will receive single dose of 400 mg albendazole every three months with a total of 4 treatments.

[figure not shown]

Fig. 1: Distribution of study participants

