## **7 SELECTION AND INCLUSION OF VOLUNTEERS**

### **7.1 Inclusion criteria**

Patients eligible for the study must comply with all of the following:

- Participants will be male and female between 18-60 years old
- BMI equal to or above 25 or below 25
- Body weight > 40kg
- Last intake of ivermectin at least 4 months ago
- Last intake of anti-filarial antibiotic treatment more than 12 months ago
- Resident in the endemic study area for at least 5 years

- *O. volvulus* patients, microfilariae skin snip positive and/or PCR positive for *O. volvulus*
- *M. perstans* or *Loa loa* patients positive for microfilariae and/or PCR
- Endemic controls, judged by absence of microfilariae, palpable onchocercoma, PCR negative for *M. perstans* and *O. volvulus*. Individuals should be free of other helminth infections and possess normal eosinophil frequencies (0.5-4%).
- Good general health without any clinical condition requiring long-term medication
- Normal white blood cell counts ( $3.5-11.3 \times 10^3/\mu\text{l}$ )
- Willingness to participate in the study as evidenced by signing the Informed Consent Form or parental signature in the ICF for subjects less than 21 years

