### **8.2 Clinical examination and laboratory analyses**

Clinical examinations (Annex CRF) include:

- Medical history including a questionnaire to assess demographic data, socioeconomic factors, educational factors, and behaviour during enrolment
- Skin biopsies (2 skin biopsies of 2 mm diameter at the posterior iliac crest) to assess microfilaridermia during screening, follow-up 1 and follow-up 2
- Urine for dipstick tests (pregnancy test and urine dipstick for haematuria, proteinuria, glucosuria) and metabolic analysis during screening, follow-up 1 and follow-up 2
- Stool for helminths egg counts, including schistosome infections, *Strongyloides* larvae and protozoa during screening, enrolment, follow-up 1 and follow-up 2
- Blood prick test from volunteer's finger for diagnosis of *Mansonella*, *Loa loa* and other filarial infections and blood glucose measurements during screening, follow-up 1 and follow-up 2
- Venous blood will be used to assess white blood cell counts, differential cell blood count, malaria parasites and fasting blood glucose levels, metabolic and immunological parameters during enrolment, follow-up 1 and follow-up 2

- HbA1c, cholesterol, triglycerides, HDL-C, LDL-C, AST, ALT, ALP, CGT, adipokines, Glucagon, Insulin, C-peptide, Ghrelin, GIP, GLP-1, HOMA-IR, serum creatinine, urea and urine albumin, LBP, EndoCAB, LPS, iFABP,  $\alpha$ -2M, CRP, haptoglobin, SAA during screening (before treatment), follow-up 1 and follow-up 2
- Height, weight, waist circumference, body fat (using a weight scale body fat analyser), blood pressure, electrocardiogram measurements during screening, follow-up 1 and follow-up 2

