## 10 STATISTICAL CONSIDERATIONS

### 10.1 Sample size justification and statistical analysis

This is a partially randomized controlled open label pilot trial to gain first experience on the impact of infections with the filarial nematodes *O. volvulus* and *M. perstans* on the metabolic profile and the systemic immune response in lean and obese patients. As there is limited data that exists to inform on study design, we will use 400 persons per group (*O. volvulus* infected, *M. perstans* infected, and endemic non-helminth-infected persons) with half of the participants of each group having a BMI of  $\geq 30$  and the other half of below 25. Thus, cases (those with active worm infections) and controls (worm infection free) will be included at a case: control ratio of 1:1:1. All *M. perstans* infected patients and all *O. volvulus* infected persons will further be treated in an interventional pilot study to test the changes in the metabolic profile and the systemic immune responses following treatment with doxycycline.

Our primary endpoint will be quantitative changes in insulin resistance (HOMA-IR). The logarithmic transformed HOMA-IR values will be compared between the three obese subgroups with a two-step test procedure. In the first step a one factorial analysis of variance will be used to test the hypotheses of equal mean log(HOMA-IR) values in the three groups at a level of 5%. In case that this hypothesis can be rejected the mean log(HOMA-IR) values will be checked for equality for each pair of groups with a two-sided t-test at a level of 5% for each test. This test procedure maintains a multiple level of 5%. From literature data (33) we expect the logarithm of the HOMA-IR to be normally distributed with a standard deviation of 0.83. With the planned sample size of 200 cases per group the intended test procedure then has a power of 80% to detect a deviation of 0.3 in the mean log(HOMA-IR) values between two of these groups. This is equivalent to reduction of 25% of the HOMA-IR in comparison between these two groups.

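### Dually infected people may fill either infected group with no assignment rule, so the one-factor, species-by-species HOMA-IR test can credit one filaria's effect to another

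*Protocol*

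**What the plan says.** **Group membership.** For both the onchocerciasis group and the *M. perstans* group, section 6.3 says that people carrying *M. perstans*, *O. volvulus* or *Loa loa* together are a reserve: "co-infected individuals will be included and treated with doxycycline and albendazole, in case that not sufficient individuals with" the single infection can be found. The provision is nearly the same in both bullets. There is no upper limit, and nothing decides the group of someone who qualifies for both.

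**Controls.** The synopsis lists for group 3 only: "Negative for other filarial and helminth infections". Section 7.1 likewise ties freedom from other helminths to endemic controls, and section 10.1 describes the controls as free of worm infection.

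**Primary analysis (10.1).** In the obese subgroups, a "one factorial analysis of variance will be used to test the hypotheses of equal mean log(HOMA-IR) values in the three groups", followed on rejection by a "two-sided t-test at a level of 5% for each test". Log(HOMA-IR) is taken as "normally distributed with a standard deviation of 0.83". Infection group is the only factor.

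**Data at hand (8.2).** Skin snips, finger-prick blood and "Stool for helminths egg counts, including schistosome infections" are all examined at screening, so each person's worm status will be known.

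**The concern.** The pairwise tests are read by species: *M. perstans* against no worms, *O. volvulus* against no worms, one species against the other. A one-factor analysis supports that reading only if each infected group carries its own filaria. If a share *p* of the *M. perstans* group also carries *O. volvulus*, that group's mean includes *p* times the *O. volvulus* effect. The test cannot separate the two.

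Two errors follow. *M. perstans* can be declared to affect insulin resistance when it does not, and a real difference between the species is diluted. Without an assignment rule, *p* in each group also depends on undocumented choices made at enrolment. This is more than detail left to an analysis plan, because the protocol itself fixes both the test and the group composition.

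**Working it through.** **Inputs.** From 10.1: n = 200 obese people per group, SD 0.83, target difference 0.3, two-sided 5%. Assumed, because the protocol does not give them: the co-infected share *p*, and the size of each worm's effect.

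**The plan's own figure.** SE of a difference = 0.83 × √(2/200) = 0.083. Power of one t-test for 0.3 = Φ(0.3/0.083 - 1.96) = Φ(1.65) = 95%. Simulating ANOVA then t-test gives about 90% (third mean midway) to 94% (third mean equal to one of the pair). The stated 80% is not reproduced; it is understated. That is a separate matter, but it leaves power to spare for the fix.

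**Second filaria.** Assume *O. volvulus* shifts log(HOMA-IR) by -0.3 (the protocol's target size), *M. perstans* has no effect, and a share *p* of the *M. perstans* group carries both.

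- Spurious difference from controls = *p* × 0.3.
- Remaining difference between the infected groups = 0.3 × (1 - *p*).

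Simulated rejection rates for the full two-step procedure (n = 200, SD 0.83):

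| *p* | Spurious difference | *M. perstans* falsely differs from controls | Difference left between infected groups | Power, infected groups |
|---|---|---|---|---|
| 0 | 0 | 5% | 0.30 | 94% |
| 10% | 0.03 | about 6% | 0.27 | about 89% |
| 20% | 0.06 | about 11% | 0.24 | about 80% |
| 30% | 0.09 | about 19% | 0.21 | about 70% |
| 50% | 0.15 | about 42% to 43% | 0.15 | about 43% |

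The ANOVA step does not protect the *M. perstans* comparison here: the true *O. volvulus* effect makes it reject in at least 90% of runs at every *p* shown.

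If neither named filaria has an effect and the extra worm (say *Loa loa*) shifts the outcome by -0.3, the ANOVA step does hold rates down: about 3%, 9% and 35% at *p* = 10%, 25% and 50%, against 2.3% with no contamination.

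**Intestinal worms, only if present in the infected groups and absent in controls.** Assume 30% to 40% carriage and an effect of 0.2 to 0.3. The bias is 0.3 × 0.2 = 0.06 to 0.4 × 0.3 = 0.12. With both infected groups shifted, the two-step procedure gives about 7% to 22% false positives per infected-versus-control pair, against 2.5% with no bias.

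**Mono-infected contrast.** With n₁ = 200(1 - *p*) against 200 controls, SE = 0.83 × √(1/n₁ + 1/200):

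- *p* = 30%: n₁ = 140, SE 0.0915, power Φ(3.28 - 1.96) = 91%.
- *p* = 50%: n₁ = 100, SE 0.1017, power Φ(2.95 - 1.96) = 84%.
- *p* = 75%: n₁ = 50, SE 0.1312, power Φ(2.29 - 1.96) = 63% (62% with the exact t).

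**Indicator model at *p* = 50% of the *M. perstans* group.** Of 600 people, 200 carry *M. perstans*, 300 carry *O. volvulus* and 100 carry both. The centred sums are 200 - 200²/600 = 133.3 and 300 - 300²/600 = 150; the cross-term is 100 - 200 × 300/600 = 0. With 0.83² = 0.689, the SEs are √(0.689/133.3) = 0.072 and √(0.689/150) = 0.068, and the SE of the species difference is √(0.072² + 0.068²) = 0.099. Power for a species difference of 0.3, without the ANOVA step, is Φ(0.3/0.099 - 1.96) = 86%, where the stated procedure keeps 43%. This assumes that the two worms' effects add.

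**The case against.** **Co-infection is only a reserve.** True. The share could be near zero, and at 10% the damage is slight. But 6.3 sets no limit, 6.1 describes all three species as endemic at the site, and the synopsis lists double-infected people for treatment without the shortage condition.

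**The primary objective (5.1) concerns filarial infection in general.** A pooled contrast of any filaria against none would not be confounded by a second filaria. This stands, but 10.1 does not specify that contrast; its pairwise tests are by species.

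**Covariates belong in an analysis plan.** In part. A later plan could add terms, but as written the protocol commits to a one-factor test.

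**Stronger readings the documents do not support.**

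- A reader might infer that infected groups are openly allowed intestinal worms. Section 7.2 excludes chronic infections other than filarial ones for everyone, which can be read as barring them. Against that, only controls have an explicit helminth criterion, and 9.3 and 13.3 expect such worms among participants. The text is ambiguous.
- A reader might infer that the protocol says these worms lower HOMA-IR. Section 4.2 reports a cross-sectional association, in people who also had lower BMI, so the 0.2 to 0.3 used above is purely an assumption.
- A reader might infer that albendazole biases a follow-up comparison. All groups receive it, and 10.1 states no between-group test at follow-up.
- The looser wording of the case definition in 6.3, and the selection of controls on eosinophils and IgE, do not bear on the HOMA-IR comparison.

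**Conclusion.** The point holds for a second filaria. Sections 6.3 and 10.1 together let one species' effect be credited to another, with no rule fixing who belongs where. The size depends on a co-infection share that the protocol does not give. Under the assumed effects (-0.3 for *O. volvulus*, none for *M. perstans*), the harm is small at 10%, material at 30% (about 19% false *M. perstans* findings and 70% power between the infected groups) and severe at 50%.

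Intestinal worms are a secondary and conditional point. What can be said is that the synopsis and sections 7.1, 7.2, 9.3 and 13.3 need reconciling. The rates of about 7% to 22% apply only if such worms are present in the infected groups alone and have the assumed effect.

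**What to change.** 1. **Section 10.1:** estimate the species contrasts from a model of log(HOMA-IR) with a separate yes/no term for *M. perstans*, *O. volvulus*, *Loa loa*, and any intestinal helminth or schistosome, using the section 8.2 results. The two-step form can stay: test the *M. perstans* and *O. volvulus* terms jointly first, then each term and their difference.
2. **Alongside it:** report mono-infected people against controls, which does not need the assumption that effects add.
3. **Section 6.3:** state a fixed rule that puts each dually infected person in one group.
4. **Eligibility:** reconcile the synopsis and section 7.1 with section 7.2 on whether infected participants may carry other helminths.

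**Cost.** Wording changes, with no new measurements. The mono-infected contrast loses people exactly when single infections are scarce: power for 0.3 is about 91%, 84% and 62% at 30%, 50% and 75% co-infection. The indicator model uses everyone and partly offsets this, at the price of assuming additive effects; showing means by infection combination lets readers judge that assumption.
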